## ANTICIPATED RESULTS AND PROJECT SIGNIFICANCE

Patients with SLE often manifest flares (relapses) of their disease, which contribute to substantial clinical, financial,^41^ and societal burden and tend to trigger treatment intensification including administration of glucocorticoids. The cellular and molecular mechanisms underlying transition of SLE from inactive to active state remain incompletely understood. In view of the biological complexity of the disease, we hereby propose the utilisation of novel, high-resolution genomic technologies which enable the simultaneous profiling of gene expression and chromatin state (accessibility) in circulating blood cells of the lupus patients both during disease quiescence, flare-up, and following introduction of therapy. Through this approach, a detailed atlas of the genome will be obtained in thousands of cells assayed across consecutive time points. We will be able to characterise specific immune cell sub-populations that are altered in terms of frequency and/or functional state during SLE flare. In addition, chromatin analysis will provide novel insights into regulatory/epi-genetic drivers of perturbed transcriptomes associated with disease re-activation. Altogether, our analysis could uncover novel and biologically-relevant biomarkers for disease remission and exacerbation, as well as putative targetable genes and pathways for flare prevention and treatment.

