## AIMS OF THE STUDY

In this research study, we aim to investigate the cellular and molecular basis of flares in patients with SLE. Considering the complexity of the disease, we will utilise state-of-the-art single-cell sequencing technologies to obtain a detailed map of the transcriptional and epigenetic profiles in multiple subtypes of peripheral blood immune cells. Through a prospective biosampling protocol, we plan to simultaneously characterise gene expression and chromatin accessibility at single-cell resolution in the peripheral blood mononuclear cells (at least 3,000 to 5,000 cells per patient sample) from two (2) SLE patients assayed at three (3) consecutive time points: disease remission, flare and post-flare (after treatment modification). Our hypothesis is that specific epigenetic modifications (chromatin accessibility) direct the molecular reprogramming of specific immune cells thus contributing to SLE relapse.

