### Sample size

Considering that single-cell technologies enable the profiling of thousands of individual cells (up to 10,000 cells per sample) from peripheral blood samples, a relatively small number of patients is adequate. Since this is a pilot study, only two (2) patients will be analysed, each patient sampled on three consecutive time points: during remission or low disease activity, at the time of flare, 3 months post-flare and after treatment administration.

Patient samples of each time point will be combined and profiled in a separate 10x Multiome library. To identify two eligible patients, a total 20 SLE patients who meet the aforementioned inclusion criteria will be monitored clinically over a period of 12 months.

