### Clinical monitoring and bio-sampling protocol

Enrolled patients will be monitored every 3–4 months for a total period of 12 months. On each visit, routine laboratory, serological (C3/C4, anti-dsDNA) and urine tests will be performed, and disease activity will be quantified by the validated indices: a) SLE Disease Activity Index-2000 (SLEDAI-2K)^26^ and b) Physician Global Assessment (PhGA; scale 0–3).^27^ For the detection and quantification of flares, the SELENA-SLEDAI Flare Index (SFI) will be employed,^27^ following minor modifications as outlined in **Table 1**. Patient history, physical examination and any relevant laboratory or imaging tests will be considered to exclude any flare-mimics such as infection or drug adverse effect. Administered medications and dosages will be recorded.

**Table 1. T1:** Modified SELENA-SLEDAI Flare Index.^27^

**Moderate flare**	**Severe flare**
Increase in SLEDAI by ≥3 points (but not to >12)	Increase in SLEDAI to >12 points
New or worse: discoid, photosensitive, profundus, cutaneous vasculitis or bullous lupus rash, nasopharyngeal ulcers, serositis, arthritis, fever	New/worse: neurological lupus, vasculitis, nephritis, myositis, platelet <60.000/μL, haemolytic anaemia (Hb <7 g/L or ↓ Hb > 3 g/L)
Increase or added prednisone, but to a dose <30 mg/day	Increase or added prednisone to a dose ≥30mg/day, or pulses of intravenous methylprednisolone
Added NSAID or antimalarials (for SLE activity)	Added cyclophosphamide, azathioprine, methotrexate or mycophenolate, or new biological drugs (rituximab, belimumab) for SLE activity, or hospitalization
Increase in PhGA by ≥1 (but not to >2.5)	Increase in PhGA to >2.5

SLEDAI, SLE disease activity index; NSAID, nonsteroid anti-inflammatory drugs; PhGA, physician global assessment; Hb, haemoglobin.

Upon inclusion to the study, all patients will donate a first blood sample (15 ml) obtained by venipuncture (low disease activity/remission stage). During follow-up, a second blood sample will be obtained from two SLE patients who will develop moderate or severe flare according to the SFI (flare stage). Those patients will be managed for active disease at the discretion of the treating physician and in line with the EULAR recommendations.^28^ Three months after therapeutic intervention of the flare, a third blood sample will be collected (post-flare stage).

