### Isolation of peripheral blood mononuclear cells and single-cell RNA-seq/ATAC-seq

We will assay blood as a relevant and easily accessible tissue to define complex inflammatory signatures.^29,30^ Venous samples (2 patients x 3 time-points, 6 in total) will undergo Ficoll density centrifugation for isolation of peripheral blood mononuclear cells (PBMCs). In SLE, the PBMCs fraction also includes circulating neutrophils,^31^ which are relevant to disease pathogenesis. Single-cell suspensions will be prepared on microplates through the robotic Fluidigm C1 system, followed by purification of RNA and chromatin from the cell nuclei.^32^ Genomic material will be processed for library synthesis (DNA for chromatin, cDNA for gene expression) and analysis by the chromium-based (10x) single-cell multiome ATAC (Assay for Transposase-Accessible Chromatin) & gene expression.^32–34^ Next-generation sequencing will be carried out at the Genomic Facility, IMBB-FORTH.

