### Bioinformatics and data analysis

We will create a single-cell transcriptomic and epigenomic atlas followed by modularity optimisation to detect immune cell clusters across patient groups and time-points.^35,36^ Differential gene expression between pertinent immune cell clusters, coupled with functional enrichment analysis, will characterise the cellular states and dedicated transcriptional programs predisposing to flares. Chromatin accessibility data will help to disentangle the regulatory programs governing the transition to active SLE, guided by the cell-to-cell linkage between modalities (scRNA-seq, scATAC-seq) and the cell-state annotations of the transcriptome atlas. Using the scATAC-seq data, we will characterise our immune cell clusters, and determine high resolution cell sub-clusters with unique chromatin accessibility profiles. Open chromatin regions (OCRs) will be subjected to functional enrichment analysis (LOLA, GREAT tools) to infer their putative regulatory roles.^37,38^ Also, mapping of transcription factor (TF) binding sites (TFBS) motifs^39^ will reveal enrichment of specific TFs involved in the acquisition of a primed state of immune cells. Correlation between gene expression, TF expression and motif accessibility will identify flares-predisposing Gene Regulatory Networks (TF-to-gene promoter/enhancer relationships). Finally, reconstruction of immune cell lineage differentiation and cell maturation trajectories will delineate the cellular dynamics and underlying states during SLE re-activation*.*^35,40^ Collectively, our analysis will decipher how gene regulatory reprogramming in immune cells triggers flare initiation. We will also test the reversibility of these molecular/regulatory programs in the post-flare samples.

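### Cell-type frequencies at flare will be relative shares of recovered mononuclear cells, so a fall in one type looks like a rise in the others unless a same-day blood count anchors them

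*Protocol article*

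**What the plan says.** All places are in the protocol article.

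- **Anticipated Results and Project Significance** promises to "characterise specific immune cell sub-populations that are altered in terms of frequency and/or functional state during SLE flare". It gives frequency no unit or denominator.
- **Aims of the Study** sets the yield at "at least 3,000 to 5,000 cells per patient sample"; **Sample size** mentions "up to 10,000 cells per sample".
- **Sample size** states that "only two (2) patients will be analysed, each patient sampled on three consecutive time points", and that "Patient samples of each time point will be combined and profiled in a separate 10x Multiome library".
- **Isolation of peripheral blood mononuclear cells** states that "Venous samples (2 patients x 3 time-points, 6 in total) will undergo Ficoll density centrifugation". It adds that in SLE this fraction also contains neutrophils.
- **Bioinformatics and data analysis** plans "modularity optimisation to detect immune cell clusters across patient groups and time-points", followed by differential expression, enrichment, chromatin, network and trajectory analyses. No step converts cluster sizes to cells per volume of blood.
- **Clinical monitoring and bio-sampling protocol** states: "On each visit, routine laboratory, serological (C3/C4, anti-dsDNA) and urine tests will be performed". Table 1 in that section uses platelet and haemoglobin thresholds, which implies a blood count. A differential is not named, and no count is tied to the day of a research draw.

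**The concern.** The number of cells captured reflects how the library is prepared, not how many cells the patient has per litre of blood. Only the relative sizes of the clusters can be read from it. If one cell type falls between remission and flare, every other type takes a larger share even when its true number is unchanged.

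The contrast is open to such shifts. It compares quiescent disease, flare, and three months after the flare is treated, and several flare criteria in Table 1 are themselves changes of treatment. That activity or treatment alters lymphocyte totals in these patients is an assumption, because the article gives no counts.

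At stake is the frequency part of the promised output. A cluster described as expanded at flare could be put forward as a feature of flare when the real event is loss of a different cell type.

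**Working it through.** **The article's own figure.** 2 patients x 3 time points = 6 samples, as stated. The article gives no alpha, power or effect size, so there is no sample-size calculation to check. The question is one of proportions.

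**Formula.** Share of type k = N_k / (sum of all N), where N is the true count per volume of blood.

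**Illustration 1** (assumed counts, x 10^9/L; monocytes constant at 0.4):

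| Lymphocytes | Monocyte share | Ratio to baseline |
|---|---|---|
| 1.6 (baseline) | 0.4/2.0 = 20.0% | 1.00 |
| 1.1 | 0.4/1.5 = 26.7% | 1.33 |
| 0.8 | 0.4/1.2 = 33.3% | 1.67 |

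**Illustration 2** (assumed counts per µL, T/B/NK/monocytes; only T cells fall). Apparent rise of each unchanged type:

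| Fall in T cells | From 1000/200/200/400 | From 700/100/100/500 |
|---|---|---|
| 20% | 1.12 | 1.11 |
| 30% | 1.20 | 1.18 |
| 50% | 1.38 | 1.33 |
| 70% | 1.64 | 1.54 |

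**Why the shares cannot settle it.** Start from 1000/200/200/400, total 1,800.

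- T cells halved, others fixed: 500/200/200/400, total 1,300.
- T cells fixed, others doubled: 1000/400/400/800, total 2,600.

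Both give shares of 38.5/15.4/15.4/30.8%. Only the total separates them, and the captured cells do not carry the total. This holds whatever counts are assumed.

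**More cells do not help.** For the 50% fall, the monocyte share goes from 400/1,800 = 22.2% to 400/1,300 = 30.8%. A naive two-proportion z that treats cells as independent is (p2 - p1)/sqrt(2 p(1 - p)/n), with p the mean of the two shares. It is 7.5 at n = 3,000, 9.7 at 5,000 and 13.7 at 10,000. The artefact only looks more certain.

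**Does a count repair it?** Share x same-day mononuclear count: 22.2% x 1,800 = 400 before and 30.8% x 1,300 = 400 after, a ratio of 1.00. The same holds in every scenario of illustration 2. Two conditions apply.

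- *Donor assignment.* Suppose one patient goes from 1000/200/200/400 to 500/200/200/400 and the other stays at 700/100/100/500, with equal numbers of cells from each. Pooled share x mean count then gives 1.04 for B and NK cells and 0.97 for monocytes, where the truth is 1.00.
- *Neutrophils.* If mononuclear cells stay at 1,800 per µL but 50, 200 or 500 neutrophils per µL enter the recovered fraction and the denominator, the rescaled monocyte ratio is 1,800/1,850 = 0.97, 1,800/2,000 = 0.90 or 1,800/2,300 = 0.78. Using mononuclear cells only returns 1.00.

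**The case against.** The strongest objection is that the article describes no comparison of cell abundance. Frequency appears once in this sense, among anticipated results, and the methods concern clustering, expression and chromatin. A relative frequency is a legitimate descriptive quantity, and its scaling could be left to the full protocol. This stands in part: the article does not say that shares will be read as expansion or loss, and nothing it states is numerically false. But altered frequency is a promised output, the described assay can supply only shares, and a better scale is available at little cost.

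A reader might infer more than the documents support:

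- *That the plan will report cell frequencies as reversed after the flare.* The reversibility test concerns molecular and regulatory programmes, not cell numbers.
- *That the shares will give the wrong direction.* The illustrations show an apparent change where there is none, not a reversed sign, and the article gives no counts from which to argue one.
- *That usable same-day counts already exist.* Table 1 implies a blood count at visits, but not lymphocyte and monocyte counts on the draw day.
- *That both patients must agree before a change is called.* Nothing in a two-patient descriptive pilot requires that rule.

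It is also true that a blood count does not correct unequal loss of cell types during Ficoll separation or preparation of nuclei.

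**Conclusion.** The point holds as a cheap improvement to one promised output, not as an error in the core analysis. Cluster frequencies from this assay are relative and cannot by themselves show that a cell type has expanded or been depleted in blood.

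The ambiguity follows from the assay and needs no assumption about counts. Its size does: the apparent expansion is 1.33- to 1.67-fold in the first illustration and 1.11- to 1.64-fold in the second, all on assumed counts. That the data will be shares is an inference, but the only reading the described capture allows.

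Expression and chromatin results within clusters, which carry the study hypothesis, are unaffected, as is the reversibility test of molecular programmes.

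**What to change.** 1. State that cluster frequencies are relative, and name the denominator.
2. For each of the six analysed draws, record the same-day lymphocyte and monocyte counts from the routine blood count, requesting the differential if it is not already included. The two patients are not known at enrolment, so the first count has to be recorded for all 20: 20 + 2 flare + 2 post-flare = 24 counts.
3. Assign the cells in each pooled library to their donor.
4. For each patient, compute each cluster's share among mononuclear cells only, with neutrophils out of the denominator. Multiply it by that patient's lymphocyte plus monocyte count, and report both scales.
5. Describe a cluster as expanded or depleted only when the absolute scale supports it. Report neutrophil clusters as fractions only.
6. State as a limitation that cell-type-specific loss in Ficoll separation or nuclei preparation is not corrected.

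The cost is a differential that may have to be requested on the draw day, donor assignment in the pooled libraries, and a short additional calculation. The counts should be arranged before sampling starts, because a count not taken on the day of the draw cannot be recovered later.
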